## Abstract

Chronic low back pain (CLBP) presents as a widespread medical issue which severely affects personal health status while generating substantial economic expenses. Traditional treatment methods often have limited efficacy, necessitating the exploration of alternative therapies such as yoga and mindfulness-based stress reduction (MBSR). This study aims to compare the efficacy of Sphinx pose yoga and MBSR in managing CLBP. The focus is on evaluating improvements in pain intensity, functional disability, quality of life, heart rate variability and physiological markers associated with CLBP. This multicentre parallel-arm randomised controlled trial will compare the efficacy of yoga to MBSR for CLBP in healthcare providers. Participants will be randomly assigned to one of four groups: Sphinx pose yoga therapy (Group A), MBSR (Group B), usual care (Group C) and a combined yoga-MBSR intervention (Group D). Each intervention will last 12 weeks. Primary outcomes include pain intensity, functional disability (Oswestry Questionnaire) and physiological markers (cortisol, β-endorphins, substance-P, interleukin-6, C reactive protein). Secondary outcomes encompass quality of life (WHO Quality of Life), stress (Sadaf Stress Scale), depression (Beck Depression Inventory), anxiety (Generalised Anxiety Disorder-7) and heart rate variability. Data will be collected at baseline (week 0), at the end of the intervention (week 12) and 12 weeks after the intervention (week 24). Trial registration number NCT06910982.

WHAT IS ALREADY KNOWN ON THIS TOPICChronic low back pain (CLBP) is a widespread condition that impairs quality of life and contributes significantly to socioeconomic costs.Healthcare providers are particularly vulnerable to CLBP due to the physical and emotional demands of their profession.Conventional treatments often have limited effectiveness, leading to growing interest in alternative therapies like yoga and mindfulness-based stress reduction (MBSR).Yoga and MBSR have shown promise individually for managing chronic pain, but their specific comparative effects on CLBP, particularly in healthcare providers, are not well established.

WHAT THIS STUDY ADDSThis study is among the first to systematically compare yoga, MBSR and their combination against usual care in a randomised controlled multicentre trial specifically among healthcare providers with CLBP.It uniquely integrates clinical (pain, disability, quality of life, mental health) and psychophysiological outcomes (inflammatory biomarkers and heart rate variability) to offer a comprehensive evaluation of interventions.By focusing on a specific yoga posture (Sphinx pose) and structured mindfulness practice, it provides nuanced insights into targeted non-pharmacological treatments for CLBP.HOW THIS STUDY MIGHT AFFECT RESEARCH, PRACTICE OR POLICYResults could establish evidence-based, non-pharmacological treatment protocols for managing CLBP among healthcare workers, a high-risk population.It may encourage broader integration of mind-body interventions like yoga and MBSR into clinical guidelines for chronic pain management.The use of physiological markers and heart rate variability could influence future research designs, encouraging the adoption of more objective biomarkers alongside self-reported outcomes.Findings may support policy shifts toward preventive care strategies in occupational health settings, reducing the burden of CLBP-related disability.

## Introduction

 Chronic low back pain (CLBP) is a prevalent global health issue with varying prevalence rates across different populations. In Turkey, the lifetime prevalence of CLBP was reported as 13.1%.^1^ A study in Northern India found a prevalence of 16.1% among adults.^2^ In KwaZulu-Natal, South Africa, the prevalence was 18.1%, with women having a higher rate than men.^3^ In Benin, the overall prevalence was 35.5%, with rural areas (40.2%) showing higher rates than urban areas (30.68%).^4^ Common risk factors for CLBP include increasing age, being underweight or overweight, lack of physical activity, smoking, alcohol consumption, manual work and poor posture.^2^,^4^ Other associated factors include education level, marital status and working status.^4^

CLBP has complex pathological mechanisms involving peripheral and central systems, with inflammation playing a crucial role.^5^ Studies have shown elevated levels of pro-inflammatory biomarkers in patients with CLBP, including C reactive protein (CRP), interleukin-6 (IL-6) and tumour necrosis factor-α.^6 7^ These inflammatory markers are associated with increased pain intensity and central sensitisation.^5^ However, the inflammatory profiles may differ based on racial background, with non-Hispanic black and non-Hispanic white individuals showing distinct patterns of biomarker associations with pain outcomes.^6^ Anti-inflammatory markers like IL-4 and IL-10 have also been found to have inverse relationships with CLBP symptoms.^6 7^ These findings highlight the importance of considering inflammatory biomarkers in understanding CLBP pathophysiology and developing targeted treatments.

Recent studies have explored the relationship between CLBP and heart rate variability (HRV). Evidence suggests that patients with CLBP exhibit reduced HRV and sympathetic predominance compared with healthy controls.^8^ During passive viewing of daily activity photographs, patients with CLBP showed significant changes in HRV frequency domains, increased pain sensitivity and higher pain intensity.^8^ In older adults with CLBP, emotional self-efficacy was found to moderate the relationship between low-frequency HRV and physical functioning.^9^ Interestingly, a comparison between chronic neck pain and patients with CLBP revealed insignificant differences in autonomic dysfunction.^10^ However, disability and self-efficacy correlated with HRV in patients with neck pain, while catastrophising and kinesiophobia showed stronger correlations in patients with CLBP. These findings highlight the complex interplay between chronic pain, autonomic regulation and psychological factors, suggesting potential avenues for intervention and further research.

Conventional therapies include pharmacological and non-pharmacological approaches, but their effectiveness is not always optimal.^11^ Recent guidelines recommend a multimodal management approach, combining non-pharmacological treatments such as exercise therapy, physical activity and education with pharmacological interventions in selected cases.^12^ Experts have found that yoga functions as a successful treatment method for CLBP, although it extends its benefits above classic physical exercise methods. Yoga demonstrates its ability to decrease pain along with disability and medication needs while boosting spinal flexibility and quality of life for patients with CLBP according to research.^13^ Yoga’s comprehensive approach, incorporating postures, breath regulation, mindfulness and meditation, may contribute to its effectiveness.^13 14^ Furthermore, mindfulness-based stress reduction (MBSR) and other meditation-based therapies are also found effective in managing CLBP. A meta-analysis found that MBSR significantly improved physical function in patients with CLBP at 8 weeks and 6 months follow-up.^15 16^

Building on our previously published research demonstrating the effectiveness of Sphinx pose yoga in managing CLBP, we have now designed a multicentre randomised controlled trial to compare the efficacy of Sphinx pose yoga with MBSR in healthcare providers (HCPs) with CLBP. This study will assess outcomes including pain intensity, functional disability, inflammatory biomarkers and HRV, aiming to generate robust evidence for optimising non-pharmacological interventions and improving the quality of life in individuals affected by CLBP.

## Methodology

### Study design

This multicentre parallel-arm randomised controlled trial will compare the efficacy of yoga to MBSR for CLBP. The study will have four parallel arms: Group A (yoga therapy), Group B (MBSR), Group C (usual care) and Group D (combined yoga and MBSR). Participants will be randomised into these groups and receive the respective interventions for 12 weeks.

### Participants

HCPs with CLBP will be recruited from various healthcare facilities.

### Sample size calculation

The sample size calculation is based on findings from our prior randomised controlled trial evaluating Sphinx pose yoga therapy in healthcare professionals with CLBP.^17^ In that study, participants in the yoga group showed a significant improvement in functional disability, with a mean reduction of 4.4 points on the Oswestry Disability Index (ODI) and an SD of 3.69, corresponding to an effect size (Cohen’s d) of approximately 1.2. For the current study, we have conservatively assumed a smaller effect size of 0.6 to ensure adequate power even if the true effect is more modest. This value is consistent with effect sizes commonly reported in the literature on mind-body interventions such as yoga and MBSR for CLBP. Using a significance level of 0.05 and a power of 0.80, the required sample size is 44 participants per group. To account for a potential 20% dropout rate, the final sample size has been increased to 55 participants per group, totalling 220 participants across the four study groups (figure 1).

**Figure 1 F1:**
[figure not shown]
Study flow. MBSR, mindfulness-based stress reduction.

### Randomisation

Randomisation will be conducted using computer-generated sequences, stratified by key demographics (eg, age, gender).

### Blinding

Although participants and intervention providers cannot be blinded due to the nature of the interventions, all outcome assessors will be blinded to group allocation. Assessors will not be involved in the intervention delivery and will collect and score outcome measures without knowledge of the participant’s group assignment. This is especially important given the use of subjective outcomes such as pain intensity and disability.

### Eligibility criteria

#### Inclusion criteria

Both genders between 25 and 45 years of age.Subjects having low back pain complaints and have visited the healthcare provider in recent days.Numerical Pain Rating (NPR) scale score ≥2 for their pain intensity.Roland Morris Disability Questionnaire subject’s score should be ≥4.Fear Avoidance Beliefs Questionnaire work subscale score must be <19.

#### Exclusion criteria

Subjects with high risk for physical injuries during exercise.Pregnant and/or lactating women.Subjects with musculoskeletal disorders.Medical contraindications to physical activity or yoga (eg, severe cardiovascular or neurological conditions).Current psychiatric illness or history of severe depression or anxiety, defined as:Beck Depression Inventory-II (BDI-II) score >29 (severe depression), and/orGeneralised Anxiety Disorder-7 (GAD-7) score >15 (severe anxiety).Ongoing use of psychoactive medications or enrolment in other structured psychological interventions.

### Interventions

Participants will be randomly assigned to one of four intervention groups (see table 1).

**Table 1 T1:** Detailed intervention protocols and session schedules across study groups

Group	Intervention	Description	Duration/frequencies/sessions
Group A	Sphinx pose yoga therapy	Participants will engage in Sphinx pose yoga therapy, focusing on back extension poses. The programme follows a simplified protocol aimed at improving accessibility, adherence and safety, especially for high-risk occupational groups.^17^ Sessions include warm-up stretching, targeted back extension and cool-down, with a focus on minimalism to ensure clinical benefit.	Frequency: 3 times per week for 12 weeks
			Session duration: 40 min per session
			Total sessions: 36 sessionsTotal contact time: 24 hours
Group B	MBSR (mindfulness-based stress reduction)	Participants will engage in a structured MBSR programme, including mindfulness meditation, body scan exercises, gentle yoga-based movements and group discussions. The programme follows the standard 8-week MBSR curriculum, extended to 12 weeks to match the duration of other interventions.^31^ Participants will be encouraged to practise daily at home using guided recordings.	Frequency: 1 session per week for 12 weeks
			Session duration: 2 hours per session (weeks 1–8), 1 hour per session (weeks 9–12)
			Total sessions: 12 sessionsTotal contact time: 20 hours
Group C	Usual care	Participants will receive guidance based on The Back Book, which includes advice on remaining active, avoiding prolonged rest and using simple pain control methods like over-the-counter analgesics. The approach encourages low-impact exercises (eg, walking, swimming) and basic stress reduction strategies, such as relaxation and breathing techniques.	Frequency: As per individual need, based on standard care guidelines
			Duration: 12 weeks
			Total sessions: Minimal contact, no structured sessions
Group D	Combined yoga and MBSR	Participants in Group D will receive a comprehensive, multimodal intervention consisting of full-dose Sphinx pose yoga therapy and a standardised mindfulness-based stress reduction (MBSR) programme. This design aims to evaluate the additive or synergistic benefits of combining two evidence-based approaches targeting both physical and psychological dimensions of chronic low back pain without compromising the integrity of either protocol. Sessions will be scheduled on non-consecutive days to minimise participant fatigue and optimise engagement.	Frequency: Yoga: three times/week MBSR: once a week Duration: Yoga: same as Group A MBSR: same as Group B Total sessions: 36+12=48Total contact time: 24+20=44 hours

### Outcome measures

Outcome measures will be assessed at baseline (week 0), at the end of the intervention (week 12) and 12 weeks after the intervention (week 24).

#### Primary outcomes

NPR Scale: The NPR Scale is a widely used tool for assessing pain intensity.Oswestry Low Back Pain Disability Questionnaire^18^: ODI is considered a standard to assess low back functionality.Physiological markers: Cortisol, β-endorphins, substance-P, IL-6 and CRP.

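### Seven unranked primary outcomes at two visits, but a sample size and 80% power worked out for a single two-group test at an undivided 0.05

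*Protocol article*

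**What the plan says.** The Primary outcomes section lists the NPR scale, the Oswestry questionnaire and a third entry, "Physiological markers: Cortisol, β-endorphins, substance-P, IL-6 and CRP". That makes seven primary variables, and the Abstract gives the same set. No order is stated among them. The Outcome measures section schedules all outcomes at baseline and twice afterwards, "at the end of the intervention (week 12) and 12 weeks after the intervention (week 24"), without making either later visit the primary one.

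The Study design section sets four arms: yoga, MBSR, usual care and the combination. The aim given there, in the Abstract and at the end of the Introduction is yoga compared with MBSR. The box on what the study adds also speaks of comparing the active arms with usual care.

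The Sample size calculation section contains one calculation. It starts from the earlier trial's yoga group, with "a mean reduction of 4.4 points on the Oswestry Disability Index (ODI) and an SD of 3.69", then says "we have conservatively assumed a smaller effect size of 0.6". It concludes: "Using a significance level of 0.05 and a power of 0.80, the required sample size is 44 participants per group". The allowance for dropout gives 55 per group and 220 in total.

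**The concern.** The primary list and the sample size describe two different trials. The list allows any of seven outcomes, at either of two visits, to be the primary result. The calculation allows one test and spends the whole 0.05 on it.

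One of two things then follows. If every primary outcome is judged at 0.05, the error rate for the primary claim is well above 5%, and a single nominally significant biomarker could be reported as a positive primary finding. If alpha is divided later, the power stated in the protocol no longer describes the trial. The article expects its results to inform treatment protocols, guidelines and occupational health policy, so the meaning of a positive primary result should be settled before data are seen.

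**Working it through.** **Inputs from the protocol article.** Effect size 0.6, alpha 0.05, power 0.80, 44 completers per group, 20% dropout (Sample size calculation); seven primary outcomes (Primary outcomes); two post-baseline visits (Outcome measures); four arms (Study design). Sidedness is not stated. Two-sided is assumed because it returns the protocol's 44, whereas one-sided gives 35.

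**Inputs assumed.** The documents give no correlations. I take the correlation between outcomes as 0 to 0.5 and between visits as 0.6.

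**1. The plan's own figure.**
- Effect in the earlier trial: 4.4 / 3.69 = 1.19, about 1.2; half of that is 0.6.
- n per group = 2 × (1.960 + 0.842)² / 0.6² = 43.6, so 44.
- Dropout: 44 / 0.8 = 55; 55 × 4 = 220.
- Power at 44 per group: 80.4% by normal approximation, 79.5% by t-test.

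The arithmetic is correct. It is the arithmetic of one outcome, one pair of arms and one visit.

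**2. If each primary outcome is tested at 0.05.** With seven independent outcomes, one contrast and one visit, the chance of at least one false positive when nothing differs is 1 − 0.95⁷ = 30.2%. For correlated outcomes and shared arms I simulated arm means under no effect:

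| Tests made at 0.05 | Chance of at least one false positive |
|---|---|
| Yoga vs MBSR, one visit | 23-30% |
| Yoga vs MBSR, both visits | 37-47% |
| Three contrasts with usual care, one visit | 49-61% |

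The lower end of each range is outcome correlation 0.5 and the upper end is 0. At a correlation of 0.7 the first row falls to about 18%. One overall four-arm test per outcome at one visit behaves like the first row: 24-30% for correlations of 0.5 to 0.

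**3. If alpha is split over the seven outcomes.**
- Alpha per outcome: 0.05 / 7 = 0.00714, critical value 2.690.
- Power at 44 per group and effect 0.6: 55% by normal approximation, 53% by t-test.
- To restore 80%: n = 2 × (2.690 + 0.842)² / 0.36 = 69.3, so 70 completers per group. With dropout, 70 / 0.8 = 87.5, so 88 per group and 352 in total, against 220 planned.

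These figures use one contrast, one visit and no baseline adjustment.

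**The case against.** **A statistical analysis plan may contain a multiplicity procedure.** This stands. The article does not say that every primary test will be declared at 0.05 or that no adjustment applies; the 0.05 appears only as a sample-size input. A reader might infer that testing is uncorrected, but the text does not establish it. What remains is on the page: an unranked primary list beside a calculation at an undivided 0.05. An unseen correction over that list would reduce the power on which the protocol bases its numbers.

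**The family of tests could be exaggerated.** A reader might count seven outcomes, six pairs of arms and two visits as 84 primary tests, and conclude that a false positive is nearly certain. No section plans all six pairwise contrasts, and the stated aim is one comparison. For that comparison at one visit the risk is 23-30%: several times 5%, but not more likely than not.

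**The power loss may be overstated.** This stands in part. The planned mixed models could use baseline values. If 0.6 is expressed in raw-score SDs and the baseline-to-outcome correlation is 0.5 to 0.7 (assumed), the effective effect size is 0.6 / √(1 − r²), or 0.69 to 0.84. Power for a seven-way split is then 69% to 88%. Adjustment could thus recover much of the loss, and at the upper end all of it. The protocol's calculation claims no such gain, does not state the SD on which 0.6 is based, and gives no correlation.

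**The 0.6 is a standardised effect, so the 80% would apply to any single continuous outcome with that effect.** This is true. It would still be the power of one test at 0.05, and the article offers no effect estimate specific to pain or to any biomarker.

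**Success might require all seven outcomes.** The error rate would then not be inflated, but nothing suggests that rule. With independent outcomes, power would be about 0.8⁷ = 21%.

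**Conclusion.** The concern holds in this limited form. The protocol declares seven co-equal primary outcomes at two unranked visits, while its 80% power, as calculated, is that of one contrast on one outcome at 0.05. Testing each primary outcome at 0.05 gives about a 23-30% chance of a false-positive primary result for yoga versus MBSR at one visit, 37-47% over both visits, and 49-61% at one visit if the three contrasts with usual care are tested instead. Splitting alpha over seven outcomes lowers power from about 80% to about 53% without baseline adjustment.

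The error rates rest on assumed correlations and on testing each outcome at 0.05, which the article does not expressly plan. The power figure rests on an effect of 0.6 and 44 completers per group. The numbers 44, 55 and 220 are themselves correct.

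**What to change.** - Name ODI at week 12, the outcome on which the trial was sized, as the single primary outcome.
- Make yoga versus MBSR, the stated aim, its first contrast at two-sided 0.05. Test the contrasts involving usual care and the combined arm afterwards, in a prespecified order or with Holm adjustment.
- Make NPR at week 12 the key secondary outcome. List the biomarkers and all week-24 results as secondary, with false-discovery-rate control.
- In Sample size calculation, state that the 80% refers to that first ODI contrast only, and that 0.6 is the difference assumed between those two arms.

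The order of contrasts matters. Putting yoga versus MBSR last, behind three contrasts with usual care, would make the main question testable only if all three active arms had already succeeded. With yoga and the combination each 0.6 better than usual care and MBSR no better, power for yoga versus MBSR would drop from about 79% to about 1%.

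The cost is a change of wording in the protocol, the registry entry and the analysis plan, with the planned 220 participants unchanged. The downside is that fewer results can be called primary and the later contrasts have less than 80% power. The biomarkers stay in the trial but lose primary status, which the sponsor may regret because the article presents them as a distinctive feature.

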#### Secondary outcomes

WHO Quality of Life (WHOQOL)^19^: WHOQOL measures the quality of life.Sadaf Stress Scale (SSS)^20^: The physical stress scale subsection of the SSS (reviewed version) will be used to assess the degree of stress in relation to physical activities and its contribution to CLBP.BDI^21^: The BDI is a questionnaire used to assess the severity of depression symptoms.GAD-7 scale^22^: The GAD-7 is a brief screening tool used to assess the severity of generalised anxiety disorder symptoms.HRV: HRV, measured through wearable devices, reflects the variation in time intervals between consecutive heartbeats and will be measured using the Alive Biofeedback and Neurofeedback Device GP8.

### Biochemical assessment

Blood samples for biomarkers (cortisol, β-endorphins, substance-P, IL-6, CRP) will be collected at three points: baseline (week 0), post-intervention (week 12) and follow-up (week 24), between 08:00 and 09:00 in a fasting state to minimise diurnal and metabolic variability. Participants will be instructed to avoid vigorous physical activity, caffeine and analgesics 12–24 hours before sampling. The collected samples will be centrifuged within 30 min and stored at −80°C. All biomarkers will be analysed using standardised ELISA kits following international protocols.

### Study timeline

Baseline assessment and participant enrolment (week 0).Intervention delivery (1–12 weeks).First follow-up (at the end of the intervention—week 12).Second follow-up (12 weeks after the intervention—week 24).

